### **5.2 Major Events**

Major Events are non treatment-related Grade 3 and 4 hematologic and nonhematologic toxicities. Treatment should be delayed for major events if AT-101 may further complicate the non-treatment related event. If a major event requires a delay of treatment, treatment must be delayed until toxicity is resolved ( $\leq$  Grade 2 or  $\leq$  Baseline). If toxicity is not resolved in  $\leq$  2 weeks, patient will be taken off treatment. ABTC office should be consulted if you are not clear on whether to continue or delay treatment.

### **5.3 Toxicity Criteria**

All toxicities will be graded according to the Common Terminology Criteria for Adverse Events v.4.0 beginning January 1, 2011. A copy of the CTCAE can be downloaded from the CTEP home page (<http://ctep.cancer.gov>). All appropriate treatment areas should have access to a copy of CTCAE version 4.0.)

### **5.4 Data Reporting**

This study will be monitored by the Clinical Data Update System (CDUS) version 3.0. Cumulative CDUS data will be submitted quarterly to CTEP by electronic means. Reports are due January 31, April 30, July 31, and October 31.

## 6.0 PHARMACEUTICAL INFORMATION

### 6.1 AT-101

|                                    |                                                                                                                                                                                                                                                                                                                                                                                                            |                               |
|------------------------------------|------------------------------------------------------------------------------------------------------------------------------------------------------------------------------------------------------------------------------------------------------------------------------------------------------------------------------------------------------------------------------------------------------------|-------------------------------|
| Chemical Name:              | R-(-)-1,1',6,6',7,7'-hexahydroxy-3,3'-dimethyl-5,5'-bis (1-methylethyl) [2,2'-Binaphthalene]-8,8'-dicarboxaldehyde acetic acid                                                                                                                                                                                                                                                                             |                               |
| Other Names:                | AT-101; R-(-)-gossypol                                                                                                                                                                                                                                                                                                                                                                                     |                               |
| Classification:             | Bcl protein inhibitor                                                                                                                                                                                                                                                                                                                                                                                      |                               |
| CAS Registry Number:        | 90141-22-3                                                                                                                                                                                                                                                                                                                                                                                                 |                               |
| Molecular Formula:          | C 32 H 34 O 10                                                                                                                                                                                                                                                                                                                                                            | M.W.: 578.7 grams/mole |
| Mode of Action:             | R-(-)-gossypol acetic acid, the levorotatory enantiomer of gossypol acetic acid, is a small molecule that induces cancer cell apoptosis by inhibiting the BH3 domain of the anti-apoptotic Bcl proteins, Bcl-2 and Bcl-xL. Also an Mcl-1 inhibitor.                                                                                                                                                        |                               |
| How Supplied:               | R-(-)-gossypol acetic acid is supplied by Ascenta Therapeutics, Inc. and distributed by the CTEP, DCTD, NCI. R-(-)-gossypol acetic acid is supplied as a 10 mg immediate release tablet in high density polyethylene (HDPE) opaque bottles containing 200 tablets. The inactive ingredients contained in each tablet are silicified microcrystalline cellulose, sodium starch glycolate, and stearic acid. |                               |
| Storage:                    | Store R-(-)-gossypol acetic acid in the refrigerator (2°C to 8°C) and protect from light.                                                                                                                                                                                                                                                                                                                  |                               |
| Stability:                  | Stability studies with the 10 mg dosage form are ongoing.                                                                                                                                                                                                                                                                                                                                                  |                               |
| Route(s) of Administration: | Oral                                                                                                                                                                                                                                                                                                                                                                                                       |                               |
| Method of Administration:   | Administer at the same time each day at least 1 hour before or after a meal. If a patient vomits after taking R-(-)-gossypol acetic acid, instruct the patient to not retake the dose. Do not crush tablets.                                                                                                                                                                                               |                               |
| Patient Implications:       | Do not take drugs, foods, supplements, or over-the-counter medications containing divalent cations (e.g., dairy products, calcium supplements, or antacids) for 2 hours before to 4 hours after each dose of R-(-)-gossypol acetic acid.                                                                                                                                                                   |                               |

### Availability

AT-101 is an investigational agent supplied to investigators by the Division of Cancer Treatment and Diagnosis (DCTD), NCI.

AT-101 is provided to the NCI under a Collaborative Agreement between Ascenta Therapeutics, Inc. and the DCTD, NCI (see Section 13).

### Agent Ordering

NCI supplied agents may be requested by the Principal Investigator (or their authorized designee) at each participating institution. Pharmaceutical Management Branch (PMB) policy requires that agent be shipped directly to the institution where the patient is to be treated. PMB does not permit the transfer of agents between institutions (unless prior approval from PMB is obtained.) The CTEP assigned protocol number must be used for ordering all CTEP supplied investigational agents. The responsible investigator at each participating institution must be registered with CTEP, DCTD through an annual submission of FDA form 1572 (Statement of Investigator), Curriculum Vitae, Supplemental Investigator Data Form (IDF), and Financial Disclosure Form (FDF). If there are several participating investigators at one institution, CTEP supplied investigational agents for the study should be ordered under the name of one lead investigator at that institution.

Agent may be requested by completing a Clinical Drug Request (NIH-986) and mailing it to the Pharmaceutical Management Branch, DCTD, NCI, [name] or faxing it to [contact]. For questions call [contact].

### Agent Accountability

Agent Inventory Records – The investigator, or a responsible party designated by the investigator, must maintain a careful record of the inventory and disposition of all agents received from DCTD using the NCI Drug Accountability Record Form (DARF). (See the CTEP home page at <http://ctep.cancer.gov> for the Procedures for Drug Accountability and Storage and to obtain a copy of the DARF and Clinical Drug Request form.)

## 7.0 PROCEDURES FOR PATIENT ENTRY ON STUDY

The ABTC ID Request and Patient Registration Form for this protocol, and the signed consent should be FAXed to the ABTC Central Office. The ABTC Central Office will fax to site the completed ID Request (ID# assigned) which will confirm patient's registration. **No patient may begin treatment until this confirmation(form) is received at the registering site. NOTE:** Confirmation of the IRB approval will be required prior to patient registration

[name].  
ABTC Central Office  
[contact]  
[contact]

## 8.0 RESPONSE ASSESSMENT

### **8.1 Criteria for Response Assessment**

Standardized response criteria are outlined below. MRI/CT scans and neurologic examinations will be used to determine the response to therapy.

Complete Response: Complete disappearance of all tumor on MRI/CT scan, off all glucocorticoids with a stable or improving neurologic examination for a minimum of 4 weeks.

Partial Response: Greater than or equal to 50% reduction in tumor size on bi-dimensional MRI/CT scan, on a stable or decreasing dose of glucocorticoids, with a stable or improving neurologic examination for a minimum of 4 weeks.

Progressive Disease: Progressive neurologic abnormalities not explained by causes unrelated to tumor progression (e.g. anticonvulsant or corticosteroid toxicity, electrolyte abnormalities, hyperglycemia, etc.) or a greater than 25% increase in the size of the tumor by MRI/CT scan. If neurologic status deteriorates, on a stable or increasing dose of steroids, or if new lesions appear on serial MRI/CT, further study treatment will be discontinued.

Stable Disease: A patient whose clinical status and MRI/CT measurements do not meet the criteria for *Complete Response*, *Partial Response* or *Progressive Disease*.

Note: Clinical and radiographic evidence of increased enhancement and/or brain edema may be attributed to either an anti-tumor response induced by the treatment or to tumor progression. In some instances, it may be apparent based on PET or MR spectroscopy that the increasing mass effect reflects tumor progression, but in other instances this may be uncertain, and in such cases, stereotactic or open biopsy of the intracranial tumor site may be indicated to assess treatment options. If a response against the tumor is the primary cause for the increasing mass effect, then the patient would be able to continue treatment as part of this protocol as long as they are able to resume protocol therapy within 4 weeks of last dose. Conversely, if the edema is caused by tumor progression, the participant would be “off treatment” and would be offered other treatment options.

## **8.2 Assessment of Response**

Timing of the Evaluation of Response to AT-101: Assessment of response to AT-101 (i.e. determining whether the patient will receive additional cycles of AT-101 after the second treatment cycle) will begin with the MRI/CT (Bi-dimensional Imaging) performed just prior to *every odd* cycle of AT-101 (within - 5 days of starting cycle). All scans are to be compared to the smallest measurement scan to date. Patients will be classified as responders if they have a minimum duration of response for 4 weeks at any time after the first treatment cycle of AT-101. If at any scheduled exam, patient has a complete or partial response, a scan must be repeated prior to the next cycle (even cycle), then return to the every odd cycle schedule. This assessment is needed to determine actual duration of response.

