## **4.2 Treatment Requirements**

All eligible patients who consent to this study must have a baseline pretreatment MRI or CT scan. This scan must be done up to 14 days prior to the initiation of treatment. This MRI will be used for determining tumor response. An MRI (with bi-dimensional measurement) is preferred for evaluating tumor size. However, if the patient is unable to undergo MR (because of presence of a pacemaker, aneurysm clip or claustrophobia), CT scans will be performed consistently and used for analysis.

Patient enrollment and commencement of protocol therapy may begin as soon as is deemed medically appropriate. The patient will then receive AT-101 as described and receive a clinical assessment every 28 days (4 weeks or 1 cycle), with bi-dimensional scans performed before every odd treatment cycle (i.e. prior to cycles 1,3,5 etc). If during any scheduled MRI, patient has a Complete or Partial Response, MRI should be repeated prior to next cycle. Patients will then return to the every odd cycle schedule. This is required to confirm duration of response. All patients will be followed for survival.

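### The reference scan for tumor response is stated in two conflicting ways (baseline in 4.2, smallest scan to date in 8.2), so gradual partial responders can be missed

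*Protocol*

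**What the plan says.** Four parts of the Protocol bear on the reference scan.

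- **Section 4.2** requires a baseline MRI or CT ("This scan must be done up to 14 days prior to the initiation of treatment") and says of it: "This MRI will be used for determining tumor response".
- **Section 8.1** defines partial response as "Greater than or equal to 50% reduction in tumor size on bi-dimensional MRI/CT scan", with steroid and neurologic conditions and a 4-week minimum. It defines progression as progressive neurologic abnormalities or a "greater than 25% increase in the size of the tumor by MRI/CT scan". Neither definition says which scan the change is measured from.
- **Section 8.2**, on response assessment, states: "All scans are to be compared to the smallest measurement scan to date". It does not separate response from progression. It adds: "Patients will be classified as responders if they have a minimum duration of response for 4 weeks". A complete or partial response calls for a repeat scan before the next cycle, and 4.2 and 8.2 both say this is to establish how long the response lasts.
- **Section 8.3** has a neuroradiologist centrally review the scans of patients showing a response and compute percent regression, again with no reference scan named.

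Section 11.3 estimates the response rate as a binomial proportion with a 95% confidence interval and takes its definition from 8.1.

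**The concern.** The smallest scan to date is a natural reference for progression. For response it gives a moving target: each partial shrinkage lowers the size from which the next 50% fall must be measured. Section 4.2 gives a fixed reference instead. Because 8.1 is silent and 11.3 points only to 8.1, nothing in the document settles which applies.

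Two sites could therefore classify the same scans differently. The error runs one way: the smallest scan to date can never exceed baseline, so using it can only make a partial response harder to reach. Later steps do not catch it, because both the repeat scan and the central review start only after a response has been recorded.

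**Working it through.** The plan gives no target response rate, power or sample size for response, so there is no stated figure to reproduce. The check is on the rule itself.

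**Inputs.** Partial response needs a fall of at least 50% (8.1). Scans are done at baseline and before each odd cycle, and a cycle is 28 days (4.1, 4.2), so on-study scans fall before cycles 3, 5, 7 and so on. The reference is baseline (4.2) or the smallest scan to date (8.2).

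**First on-study scan.** The only earlier scan is baseline, so both sections give the same reference and the same call.

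**Second on-study scan.** Set baseline to 100, the first on-study size to x and the second to y.

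- Against baseline: partial response if y ≤ 50.
- Against the smallest earlier scan: partial response if y ≤ min(100, x)/2.

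If x is 100 or more the rules agree. If x ≤ 50, a partial response was already called at the first scan. If 50 < x < 100, they disagree for every y with x/2 < y ≤ 50.

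*Example:* x = 65, y = 40.

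- From baseline: (40 − 100)/100 = −60%, a partial response.
- From the smallest earlier scan: (40 − 65)/65 = −38%, stable disease.
- With x = 65 the zone of disagreement is 32.5 < y ≤ 50, and 40 lies inside it.

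**Complete response.** The criterion, "Complete disappearance of all tumor on MRI/CT scan, off all glucocorticoids", does not depend on a reference size.

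**What follows a missed call.** The repeat scan is triggered only by a recorded response (4.2, 8.2). The table in 9.1 has no routine MRI before even cycles, and 8.3 reviews only patients showing response. The patient's next routine scan is thus 8 weeks later, before cycle 7. Re-reading the scans at analysis could reclassify the size change, but could show the 4-week duration only if a later scan exists.

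**Illustrative size, from simulation.** The assumed trajectories are not in the Protocol: mean final log size change −0.3 to −1.0, SD 0.3 to 0.5, scan noise 0.1, scans at weeks 8, 16 and 24, 20,000 patients per scenario.

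| Scenario (mean, SD) | Baseline reference | First call against smallest scan, held unless >25% rise | Relative loss |
|---|---|---|---|
| −0.3, 0.5 | 19.5% | 10.2% | 48% |
| −0.6, 0.5 | 40.7% | 25.4% | 38% |
| −0.6, 0.3 | 33.8% | 14.6% | 57% |
| −1.0, 0.5 | 70.2% | 53.5% | 24% |

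Relative loss is 1 minus the ratio of the two rates; in the first row, 1 − 0.1022/0.1949 = 48%. The columns also differ slightly in how a response counts as held at the repeat scan (at most 50% of baseline, against no more than 25% above the smallest scan). The losses show direction and rough scale; they are not forecasts.

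**Illustrative size, in patients.** The earlier racemic gossypol trial described under Rationale had 2 partial responses in 27 patients of mixed glioma histology. If that rate applied here (an assumption), 56 × 2/27 = 4.1, or about 4 responders.

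| Responders counted of 56 | Rate | Exact 95% CI |
|---|---|---|
| 4 | 7.1% | 2.0% to 17.3% |
| 3 (one missed) | 5.4% | 1.1% to 14.9% |
| 2 (two missed) | 3.6% | 0.4% to 12.3% |

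**The case against.** The case against a serious finding has four parts.

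1. **A baseline reference is stated.** Section 4.2 assigns the pretreatment scan to response. The 8.2 sentence follows text about whether a patient receives further cycles, where the smallest scan is a natural comparator. A careful reader may reconcile the two sections correctly. This is fair, but 8.2 speaks of all scans, sits in the section on response, and comes closer to the point of use than 4.2.

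2. **The repeat scan does not require a second halving.** A reader might infer from 8.2 that a tumor at 100, 45 and then 45 fails confirmation because the last change is 0%, so that almost no partial response could be confirmed and the response rate would fall to near zero. In the simulation that strict reading does give 0.00% to 0.02%. The documents do not support it: 4.2 and 8.2 both give the repeat scan the purpose of establishing duration, and neither asks for further shrinkage. The first on-study scan is measured from baseline under either section, and complete responses are untouched. What remains is narrower: the Protocol does not say what reference shows that a partial response has been maintained.

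3. **Little depends on the response rate.** It is descriptive and has no target or test. The primary endpoint is death (11.2), the interim rule uses toxicity and 6-month progression-free survival (11.4), and the decision rule uses median survival or failure rate together with toxicity (11.5). This stands and limits the severity.

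4. **A careless repair could do harm.** Redefining the progression reference as the smallest scan since the start of treatment would exclude the pretreatment scan. A tumor at 100, 120, 140 is +40% against the smallest scan to date, but (140 − 120)/120 = +17% against 120, which is under the 25% threshold. That would alter 6-month progression-free survival and off-treatment calls. This stands, and the fix must leave the progression reference as written.

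**Conclusion.** The point holds as an unresolved conflict between 4.2 and 8.2, left open by 8.1 and carried into the analysis through 11.3. Where 8.2 is applied to response, a patient whose tumor first shrinks by less than half and then ends between half of that size and half of baseline is classed as stable. Such a patient has no repeat scan and no central review.

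The bias in the response rate is downward. Its size cannot be derived from the Protocol: it depends on how many sites follow 8.2 and how many responses develop over more than one scan. If every site followed 8.2 for the first call, the relative loss under the assumed trajectories was 24% to 57%. If about 4 of 56 patients would respond, missing two halves the estimate. Both figures are illustrations. Severity is moderate, since the endpoint is secondary and descriptive.

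**What to change.** Reconcile 4.2, 8.1, 8.2 and 8.3 as follows.

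- In 8.1, state that complete and partial response are measured against the pretreatment baseline scan, including whether a partial response is maintained at the repeat scan. Align 4.2 with this.
- In 8.2, limit the existing sentence to progression and otherwise keep its wording. The smallest scan to date includes baseline, so 6-month progression-free survival and off-treatment decisions do not change.
- In 8.3, state that percent regression is computed from the same baseline scan.

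The cost is a few sentences in an amendment and a note to sites. No scan is added to the schedule; a gradual responder would simply receive the repeat scan that the Protocol already requires. For patients already enrolled, the recorded measurements can be re-read against baseline, noting any for whom the 4-week duration cannot be shown because no repeat scan was done.

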## **8.3 Quality Assurance**

The Study chairmen will be reviewing the records in detail for the following:

**Neuropathology:** The neuropathologic diagnosis of glioblastoma multiforme should be made at the respective institution. If any question arises regarding the accuracy of the neuropathologic diagnosis, slides (and pathological blocks, if necessary) will be reviewed by the central review pathologist. All patients with a documented complete or partial response will have representative pathology slides undergo central review.

**Neuroradiology:** MRI/CT (Bi-dimensional Imaging) scans of patients showing tumor response will be centrally reviewed by a neuroradiologist who will independently assess tumor size and compute percent tumor regression.

**Neuro-oncology:** The local investigator at the participating institution will communicate to the protocol chairman any unexpected neurological effects such as change in seizure frequency, alteration in neuromuscular function, alteration in cognitive function, or fluctuations in serum anticonvulsant drug levels.

**Adherence to protocol therapy:** As a quality assurance measure for the treatment delivered on this protocol, primary patient records may be reviewed. The records to be examined will be selected retrospectively and at random; complete records must therefore be maintained on each patient treated on the protocol. These records should include primary documentation (e.g., laboratory report slips, X-ray reports, scan reports, pathology reports, physician notes, etc.), which confirm that:

- The patient met each eligibility criterion.
- Signed informed consent was obtained prior to treatment.
- Treatment was given according to protocol (dated notes about doses given; any reasons for any dose modifications).
- Toxicity was assessed according to protocol (laboratory report slips, etc.).
- Response was assessed according to protocol (MRI/CT scan, lab reports, dated notes on measurements and clinical assessment, as appropriate).
- NCI Drug Accountability Records were maintained for this protocol.

